### Sample Size

This is a first-in-human phase I clinical trial aimed to obtain insight on the safety and feasibility of the treatment with the BCP-MFAT combination. We assume that no SAEs or AEs will occur, based on our clinical experience with other applications of MFAT and the well-proven safety of BCP. Upon consultation with a statistician, a sample size of 8 individuals is expected to be sufficient for this trial.

### Recruitment

Patients will be recruited from an existing database of the Hasanuddin University Dental Hospital, from general practices of Hasanuddin Dental Hospital and in the area around Makassar. Thereafter, we will determine whether the candidates fulfill the study’s inclusion and exclusion criteria. Thorough assessment and training regarding the safety measurements at the research site at Hasanuddin University Dental Hospital will be performed prior to the trial by the ethical and surgical teams.

Since we did not want to enroll children in a safety study with this novel concept in clinical practice, we chose to only include older adolescent and adult patients, being themselves capable of decision-making. Within Indonesia, this age group is more common due to cultural and religious backgrounds causing abstinence from cleft surgeries.

The trial will be conducted at Hasanuddin Dental Hospital. All participants will be asked to sign an informed consent form after risks and possible complications of the procedure (eg, bleeding, infection, cheek asymmetry, parotid duct injury, possibility of facial nerve branches injury, and—although not likely—nonclosure) were appropriately communicated with the patient. Data will be handled and stored in a coded—that is, deidentified—format, so that data cannot be traced back to the patient without a decoding key, which is stored in a locked place and only accessible to the study’s principal investigator. Implants will be offered free of charge.

### Randomization and Blinding

Since this trial comprises only 1 type of treatment, no randomization or blinding to the treatment is possible.

### Data Collection and Access

The research team will be informed about the rules and their responsibilities. All members of the research team, which will collect the data in accordance with the evaluation table (Table 1), will receive training on how data collection should be performed. The data manager will document the data in a patient-coded manner (ie, each patient will be assigned a study-specific code under which the data will be stored in order to conceal their identity), which will subsequently be handed over to the clinical evaluators and investigators. The primary end point is set at 6 months.

**Table 1 table1:** Patients’ assessments.

	Consent form	Orthopantomography	Cone-beam computed tomography or computed tomography	Physical examination	Complete blood count	Thermometry	Biopsy
Preoperative	✓	✓	✓	✓	✓	✓	
Operative day				✓		✓	
Postoperative day 1		✓		✓	✓	✓	
Postoperative day 8		✓	✓	✓	✓	✓	
Postoperative day 14				✓		✓	
Postoperative day 30				✓	✓	✓	
Postoperative day 90		✓		✓		✓	
Postoperative day 180		✓	✓	✓	✓	✓	✓

### Posttrial Care

After the primary end point assessment, the participants will be followed up for an additional period of 3 years to ensure their safety and to record whether any delayed side effect occurs as a result of treatment with the BCP-MFAT combination, as previously done in a similar study [26].

### Monitoring

Internal monitors of the Ethics and Research Committee, Faculty of Medicine, Hasanuddin University, will evaluate whether the data are accurately collected. Since negligible risk to the patient is expected as both materials (MFAT and BCP) have been tested in other clinical trials [16,17,24], no data safety monitoring board will be installed. A safety report will be submitted every year to the Medical Research Ethics Committee, Faculty of Medicine, Hasanuddin University. No interim analysis is deemed necessary.

### Amendments

If deemed necessary, amendments to this protocol will be submitted to the ethical committee and competent authority and should be approved prior to implementation to ensure the safety and integrity of participants as well as the scientific value of the trial.

### Evaluation Methods

#### Safety Assessment Based on Physical Examination and Laboratory Measurements

When an SAE occurs, it will be concluded that a combination of MFAT and BCP is not yet safe in the current setting. For AEs, if they do not occur at a higher frequency than that in patients treated with standard care (autologous bone) or can be resolved through noninvasive conventional methods (eg, analgesics or antibiotics), the combination of MFAT and BCP will be considered safe. In all other cases, combination of MFAT and BCP will not be considered safe yet.

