**Conclusions:**

In this first-in-human study, not only safety but also the histologically and radiographically assessed regenerative potential of the BCP-MFAT combination will be evaluated in an alveolar cleft model. When an SAE occurs, it will be concluded that the BCP-MFAT combination is not yet safe in the current setting. Regarding AEs, if they do not occur at a higher frequency than that in patients treated with standard care (autologous bone) or can be resolved by noninvasive conventional methods (eg, with analgesics or antibiotics), the BCP-MFAT combination will be considered safe. In all other cases, the BCP-MFAT combination will not yet be considered safe.

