## Introduction

Alveolar cleft is defined as a bone gap in the primary palate from the nasal sill to the incisive foramen [1]. The defect occurs as a result of disruption of primary palate development between 4 and 12 weeks of gestational age, specifically in the frontonasal prominence [2]. The treatment protocol varies on the basis of the following factors: timing, surgical procedure, and grafting material. Secondary alveolar bone grafting (SABG) is the most preferred and successful method that is usually performed during the mixed dentition period (6-11 years), which allows the provision of support to teeth eruption and facial growth [1]. The iliac crest as a bone graft donor for alveolar cleft reconstruction has gained popularity since it was first introduced by Schmid [3] in 1954, and, in particular, for SABG procedures because it allows harvesting of large amounts of bone for alveolar cleft surgery [4]. Other bone graft sources include the cranium, tibia, and the mandibular symphysis [5]. However, several studies have reported risks of general postoperative complications using autografts, such as pain, prolonged hospital stay, and donor site–specific complications such as scarring, cutaneous nerve injury near the iliac crest, and hematoma after harvesting the cranial bone [6-9]. Therefore, alternative materials are being evaluated for alveolar cleft surgery.

Biphasic calcium phosphate (BCP) is a bioceramic that consists of 2 materials, hydroxyapatite (HA) and β-tricalcium phosphate, mixed in different ratios [10]. It is a biocompatible, easy-to-handle, safe material with a mineral composition comparable to that of human bone tissue [10]. BCP has been mixed in vivo and in vitro with autografts, inducing factors or cells to improve its osteoinductivity [11,12], also in the fields of dentistry and maxillofacial surgery [13-15]. Although calcium phosphate ceramic is not yet considered standard-of-care, it has been used for alveolar cleft reconstruction with satisfactory results [16], reportedly providing support for teeth eruption [17].

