### Statistical Analysis

Since this is a single-arm safety study, statistical analyses will not be performed.

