Recently, calcium phosphate has been applied for alveolar cleft surgeries as well [16,17]. Patients within that study were treated at ages of 9-10 years, which is within the optimum age range for SABG [1]. However, we did not want to enroll children in a safety study with this novel concept in clinical practice. Therefore, although we realize that surgeries at a later age will (1) not make optimal use of the growth spurt and (2) may result in cases having larger or even critical size defects (which will not heal unless supplemented with grafts), we chose to only include older adolescent and adult patients, who are themselves capable of being involved in decision-making. We will perform this study in Indonesia because unoperated patients in this age group are difficult to find in Europe.

This is primarily a safety study, so the main conclusions of the study will be based on safety parameters, particularly on the occurrence of AEs or SAEs.

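### Without an SAE, the primary safety verdict passes the graft if AEs are either no more frequent than an unstated autologous-bone rate or noninvasively resolvable; 8 patients cannot support the first and the second has no frequency limit

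*Protocol article*

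**What the plan says.** Safety at 6 months is the primary outcome (Results). The verdict is set under Evaluation Methods, in Safety Assessment Based on Physical Examination and Laboratory Measurements, and has three steps.

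- Any SAE means the combination is not yet safe.
- For AEs, the combination counts as safe "if they do not occur at a higher frequency than that in patients treated with standard care (autologous bone) or can be resolved" with noninvasive conventional treatment.
- Everything else is not yet safe.

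The abstract's Conclusions repeat the comparison: "if they do not occur at a higher frequency than that in patients treated with standard care (autologous bone"), with the same alternative after it.

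Other sections bear on the rule. Randomization and Blinding confirms that there is one treatment only. Statistical Analysis says that "statistical analyses will not be performed". Sample Size says "We assume that no SAEs or AEs will occur" and that "a sample size of 8 individuals is expected to be sufficient for this trial". The Introduction mentions "risks of general postoperative complications using autografts, such as pain, prolonged hospital stay" and donor-site complications, but gives no frequency. AE Assessment classes an AE as serious or nonserious by its intensity and adds Clavien-Dindo grading.

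**The concern.** This rule decides what a first-in-human study will conclude, and it has two weaknesses.

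First, one of its conditions compares 8 patients with a number the article never gives. It does not say which autologous series is meant, which AEs count, whether patients or events are counted, or how far above the comparator counts as higher. With no control arm, nothing inside the trial can supply the figure.

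Second, the two conditions are alternatives. Without an SAE, the verdict fails only if AEs are both more frequent than the comparator and not noninvasively resolvable. AEs that are very frequent but resolvable pass by one route. Unresolved AEs that are not above the comparator pass by the other. A published statement that the graft is safe could then rest on a rule that did not test what readers would take it to have tested.

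**Working it through.** **Inputs.** n = 8, single arm (Study Design, Sample Size). The AE rule is as quoted above. The autologous-bone AE rate p0 is not stated, so 10%, 20% and 30% are assumed below to show a range. The sample size of 8 cannot be reproduced, because Sample Size gives no rate, alpha, power or precision target.

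**Step 1: the rule as logic (no SAE).**

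| AE frequency against comparator | Noninvasively resolvable | Verdict as written |
|---|---|---|
| not higher | yes | safe |
| not higher | no | safe |
| higher | yes | safe |
| higher | no | not yet safe |

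**Step 2: two cases that pass.**

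- Nonserious AEs in 8/8 patients, all cleared with antibiotics or analgesics. These pass whatever p0 is. The exact two-sided 95% lower limit is 0.025^(1/8) = 0.631, so the interval is 63% to 100%.
- One unresolved AE graded nonserious. The frequency is 1/8 = 12.5% (exact 95% CI 0.3% to 52.7%). It passes if the comparator used is 12.5% or more, taking that frequency as the one compared.

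**Step 3: when the unstated rate matters.** An SAE settles the verdict as not yet safe. No AE settles it as safe. So does noninvasive resolution of every AE. Only a nonserious AE that does not resolve noninvasively makes the verdict depend on p0.

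**Step 4: what the frequency condition can show at n = 8.** Read it as a raw comparison, with X the number of patients with an AE: the graft is called higher if X/8 > p0, with X ~ Bin(8, p).

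- p0 = 10%: P(X ≥ 1 | 0.10) = 1 − 0.9^8 = 0.570. If the true rate is doubled, P(X = 0 | 0.20) = 0.8^8 = 0.168.
- p0 = 20%: P(X ≥ 2 | 0.20) = 1 − 0.8^8 − 8(0.2)(0.8^7) = 0.497. If doubled, P(X ≤ 1 | 0.40) = 0.106.
- p0 = 30%: P(X ≥ 3 | 0.30) = 0.448. If doubled, P(X ≤ 2 | 0.60) = 0.050.

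| Assumed p0 | Most AE patients allowed | Equal graft called higher | Doubled rate passes |
|---|---|---|---|
| 10% | 0 | 0.57 | 0.17 |
| 20% | 1 | 0.50 | 0.11 |
| 30% | 2 | 0.45 | 0.05 |

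At an assumed 50%, 4 AE patients would be allowed, so the missing number largely sets the result of this condition.

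If higher meant a one-sided exact test at 5% instead, failure would need 3, 5 or 6 of 8 patients at p0 = 10%, 20% and 30%. Power against a 20-point excess would be only 0.45, 0.17 and 0.15.

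**Step 5: the best possible result.** With 0/8, the exact two-sided 95% upper limit is 1 − 0.025^(1/8) = 0.369. Even no AE patients is compatible with a true rate of up to 36.9%.

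**The case against.** The best defence is that the verdict is usually reachable, and this stands. A reader might infer that the rule cannot be evaluated at all, but Step 3 shows three situations in which it gives a definite answer. One of them, no events, is the planning assumption.

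The probabilities in Step 4 also describe the frequency condition alone. A reader might take them as error rates of the whole verdict. They are not, because failing that condition is harmless if the AEs resolve.

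A reader might also infer that any permanent nerve or duct injury would be called safe. The text does not support that: an injury graded serious is caught by the SAE sentence. The gap concerns lasting harm graded nonserious, which grading by intensity leaves possible. How the cited classification would grade such an injury cannot be seen here.

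Nor does the article say that the benchmark will be picked after the results. The full protocol may name a source, and comparing x/8 with a fixed rate needs no formal test. A source would not mend the either-or structure or the imprecision, and planning no statistical analysis means that the article foresees no statement of uncertainty.

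Finally, the benchmark could be called mismatched. Autograft figures include bone donor-site events, and standard grafting is "usually performed during the mixed dentition period (6-11 years"), whereas later surgery "may result in cases having larger or even critical size defects". This is partly a choice of benchmark. The trial graft has its own donor site in the cheek, with risks listed under Recruitment, so a total-burden comparison is legitimate. The age and donor-site differences may also pull in opposite directions. They call for separate display and do not show that every comparison is invalid.

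**Conclusion.** The concern holds in limited form and should be fixed. In the absence of an SAE, the stated rule passes resolvable AEs at any frequency, up to 8/8. It lets an unresolved nonserious AE stand or fall on a rate the article does not give. Where that rate decides, 8 patients cannot support a finding of no higher frequency: the condition misclassifies a truly equal graft about half the time (0.57, 0.50 and 0.45) and 0/8 still allows 36.9%.

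The first result follows from the wording alone. The misclassification figures rest on the assumed comparators of 10%, 20% and 30%, on independent patients, and on a raw patient-level comparison. The 36.9% needs only n = 8 and the exact binomial method.

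A reader might conclude that requiring both conditions would solve the problem. It would make the frequency condition decisive: a graft equal to an assumed 10% comparator would fail at least 57% of the time, even if every AE resolved. It would also set a clinical rule that is not for a statistical review to choose.

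**What to change.** Drop the verdict that AEs are not more frequent than with standard care. Report AEs by type and Clavien-Dindo grade as x/8 with exact 95% confidence intervals. Set descriptive autologous-bone figures beside them, with the source fixed before analysis and donor-site and recipient-site events shown separately. Amend Statistical Analysis to say that these intervals will be given.

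If a verdict is kept, fix the comparator rate, its source, the AE scope and the counting unit before analysis. The trial team should also reconcile the two conditions so that very frequent or unresolved AEs do not pass by default. The acceptable clinical threshold is theirs to set.

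The cost is a wording change in the safety assessment, the abstract and Statistical Analysis, plus a short literature table. Clavien-Dindo grading is already planned, and the Amendments section provides the route. The downside is a more cautious safety conclusion.

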#### Radiographic Analysis

To evaluate the success rate of the bone graft, the Bergland scale will be used [30]. This scale will evaluate the integrity and height of the alveolar bone graft and will classify bone height into 4 grades: grade I, bone height is almost normal; grade II, a bone height that is at least 75% of the interalveolar septum; grade III, a bone height of less than 75%; and grade IV, no evidence of bone integration [31].

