#### Histological and Histomorphometric Analysis

Histological and histomorphometric analysis will be performed for at least 3 patients who received dental implants after alveolar cleft reconstruction, in accordance with previously published procedures [32]. Briefly, the implant preparation site will be developed using a trephine burr (⌀ 2.0 mm × 10.0 mm in length) that allows biopsy specimen collection from the implant site without interfering with the regular procedure. The biopsy specimens will be fixed in ﻿4% phosphate-buffered formaldehyde, dehydrated in an ascending series of ethanol, and embedded in 80% methylmethacrylate (BDH Chemicals) supplemented with 20% dibuthylphtalate (Merck), 8 g/L lucidol CH-50 L (Akzo Nobel), and 22 μL/10 mL N,N-dimethyl-p-toluidine (Merck). The biopsy specimens will be cut into ﻿5-μm-thick sections and subjected to 2 different staining procedures (﻿Goldner’s trichrome and Tartrate-resistant acid phosphatase staining). Several histomorphometric parameters (bone volume, osteoid volume, graft volume, and number of osteoclasts) will also be measured for quantitative analysis [32]. Two trained examiners will perform the histologic and histomorphometric analyses. In case of dispute, the biopsies will be reanalyzed to reach consensus.

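### The Bergland success rate grades height in a cleft filled with bone-like mineral; it is not compared with the scheduled day-8 scan, and histology is assured for only 3 of 8 patients

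*Protocol article*

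**What the plan says.** **The measure.** Radiographic Analysis in the Protocol article opens: "To evaluate the success rate of the bone graft, the Bergland scale will be used". It continues: "This scale will evaluate the integrity and height of the alveolar bone graft and will classify bone height into 4 grades". Grades I to III are set by height: almost normal, at least 75% of the interalveolar septum, and below 75%. Grade IV means no sign of bone integration. The section names no grade as success, no visit and no imaging modality.

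**The graft.** Study Design describes a synthetic ceramic of 60% hydroxyapatite and 40% β-tricalcium phosphate with 90% porosity, mixed with microfragmented fat. The Introduction calls this class of ceramic a "safe material with a mineral composition comparable to that of human bone tissue".

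**The images.** Table 1 (Data Collection and Access) has a column for "Cone-beam computed tomography or computed tomography", ticked preoperatively, on day 8 and on day 180. Orthopantomography is ticked preoperatively and on days 1, 8, 90 and 180.

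**The tissue measure.** Histological and Histomorphometric Analysis lists "Several histomorphometric parameters (bone volume, osteoid volume, graft volume, and number of osteoclasts" as separate quantities. It commits to this analysis in at least 3 patients who received implants.

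**The use.** Efficacy is the secondary objective. Study Design promises a published report on safety and on proof of concept for bone formation.

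**The concern.** A height grade is a natural outcome after autologous bone grafting. Here the surgeon places a mineral in the gap, and the protocol itself likens that mineral to bone. Some of the height read at six months may then be the material put in at surgery. The protocol treats bone and remaining graft as different things under the microscope, but gives no corresponding rule for the images.

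Without an early postoperative reference, a good grade at day 180 has two readings: bone has formed, or the construct has kept the height to which it was filled. The scan that would show the initial fill is scheduled, but no stated analysis uses it.

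The consequence falls on the claim of regenerative potential. If Bergland grades are reported as a graft success rate beside a proof-of-concept statement, readers may take them as evidence of new bone in patients for whom no tissue evidence exists.

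**Working it through.** The protocol gives no figure for this outcome, so there is none to reproduce. The check is a comparison of sections with simple counts out of 8.

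**1. What each measure can separate**

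| Measure | Separates new bone from ceramic? | Patients assured |
|---|---|---|
| Bergland grade | No rule stated | All 8, if images are taken as in Table 1 |
| Histomorphometry | Yes: bone, osteoid and graft volumes are separate | At least 3 |

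Share with an assured tissue check: 3/8 = 37.5%. Share that may have a grade and no tissue check: (8 − 3)/8 = 5/8 = 62.5%. Three is a floor, so 62.5% is the largest possible gap, not the expected one.

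**2. What the day-8 scan would add**

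Suppose both scans are graded by the same rules:

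- Same high grade on both days: the day-180 grade may simply reflect the initial fill. This fits retained ceramic, new bone, or a mixture.
- Lower grade on day 180: the construct has lost height. The images alone do not say whether ceramic or bone was lost.
- Higher grade on day 180: the initial fill alone does not account for the grade.

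With only the day-180 grade, these three cases cannot be told apart. With both, the third is separated from the first. The first still does not show new bone.

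**3. Effect of the unnamed success grades**

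Each patient whose status depends on the cut-off moves the rate by 1/8 = 12.5 points. As an assumed example, take four patients in grade I, two in grade II and two in grade III:

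- Success = grade I only: 4/8 = 50%, exact (Clopper-Pearson) 95% interval 16% to 84%.
- Success = grade I or II: 6/8 = 75%, exact 95% interval 35% to 97%.

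The same eight images give rates 2 × 12.5 = 25 points apart. Even 8/8 has an exact 95% interval of 63% to 100%, so the rate is imprecise under any cut-off. This step is subsidiary: an unnamed cut-off alone would be a detail that a full protocol could supply.

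**The case against.** **The ceramic may not pass for bone.** The Introduction's remark concerns mineral composition, in a sentence about biocompatibility. The documents give no radiodensity, resorption rate or appearance at six months. The graft is highly porous and mixed with fat, and the scale also considers integrity, with grade IV tied to integration. This stands against certainty. A reader might infer that residual ceramic would be scored as regenerated bone, or that 8/8 success could be reported with no regeneration. The documents show neither: that would require every cleft to be filled to normal height, no loss by day 180 and complete indistinguishability. What remains is that ceramic could contribute and the grading has no rule to prevent it.

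**Early postoperative images exist.** A reader might infer that the trial lacks a postoperative baseline. It does not: Table 1 schedules orthopantomography on day 1 and CBCT/CT on day 8. The point is only that the stated grading does not refer to them.

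**Efficacy also rests on histology.** This is correct, and Table 1 shows a day-180 biopsy without restriction. But the section that governs the analysis assures only 3 patients, and those are patients who received implants.

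**Blinding.** The protocol says "no randomization or blinding to the treatment is possible". A reader might take this as ruling out masked reading. It concerns treatment, and with one treatment it is right. It leaves masking to scan date open. A preoperative image of an ungrafted cleft could hardly be masked.

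**An article condenses.** Visit, modality, readers and cut-off may be in the full protocol. With 8 patients all four grades can be listed and any cut-off applied. This stands for the cut-off as an isolated omission. It does not answer the choice of a height grade as the success measure for this material.

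**The remedy is partial.** Stable height from day 8 to day 180 fits either new bone or retained ceramic. This stands, and is why the fix also limits the claim.

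**Conclusion.** The point holds in a limited form. The protocol measures graft success by bone height in a cleft filled with a calcium phosphate that it likens to bone mineral. It states no comparison with the day-8 scan, and assures the one measure that separates bone from graft in 3 of 8 patients. As written, the proof-of-concept report could credit retained ceramic as bone in up to 5 of 8 patients (62.5%).

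This rests on two assumptions: that residual ceramic is present and visible at six months, which separate measurement of graft volume in the biopsies makes plausible but does not prove; and that histology may stop at the stated minimum. The size of any bias in the grade cannot be estimated from the documents.

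The effect is confined to the secondary efficacy statement. The Discussion rests the main conclusions on adverse events, and nothing here changes them.

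**What to change.** In Radiographic Analysis:

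1. Grade the day-8 and day-180 CBCT/CT by the same rules, using the existing evaluators, with the dates of the postoperative scans masked.
2. Report each patient's day-180 grade beside the day-8 grade, with the change in construct height.
3. List all four grades as x/8. Name the success grades before grading. The article places the trial in follow-up, so if grading has begun, label the choice post hoc.
4. Describe the radiographic result as construct height. The Results section already speaks of grading the bone construct, so the wording change is small.
5. Claim bone formation only for patients whose histomorphometry supports it, and state how many of the 8 that is.

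No extra imaging, biopsy or change to treatment is needed. The cost is a few additional readings of scheduled scans and a narrower efficacy claim. The day-8 comparison shows whether a grade merely reflects the initial fill; it does not by itself prove new bone, so item 5 is needed as well.
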